#### Data collection

Outcome data will be collected via an online survey using Qualtrics software (Version 2016). The survey containing the outcome measures for the trial will be emailed to participants at two data collection points: at baseline (Time point 1), and 12 months later (Time point 2). Participants will complete the online survey in their own environments, which could be home, work, or school. Demographic information will be collected from parents at Time point 1. This information will include the adolescent’s age, gender, year level at school, and their residential postcode (to determine socioeconomic status). It is anticipated that completing the online outcome measures will take 30–45 min each time. Participants will be given a leeway of two months after each scheduled data collection point to complete the outcome measures. Participants will be reminded, as needed, by the primary researcher via telephone and email to complete the outcome measures. The trial commenced on 26 November 2015 (Time Point 1), and data collection for the post-measures began on the 26 November 2016 (Time Point 2).

The Social Responsiveness Scale-Second Edition (SRS-2) [48] will be used to classify autism severity. Parents will complete the School Age Rating Form, which is designed for children aged 4–18 years. The SRS-2 consists of 65 items and can be administered in 15–20 min. The scale results in a total score and a *t*-*score*, which can be used as an index of severity of social deficits on the autism spectrum. Scores can be interpreted as falling into one of the following four categories: within normal limits, mild deficit, moderate deficit, and severe deficit. The scale has been standardized using a nationally representative sample, and has strong psychometric properties including high internal consistency (α = .95); construct validity (two strong factors); test–retest reliability (*r* = .88–.98); and interrater reliability (*r* = .91 between mothers and fathers) [48]. Studies have shown that the SRS-2 can detect clinically meaningful and statistically significant differences between typically developing children and those diagnosed with autism [54]. Additional independent variables for this trial will be comorbidities (including mental health), gender, age, and socioeconomic status.

#### Outcome measures

Outcome measures were determined based on a literature review of all suitable measures and their psychometric properties. Outcome measures were chosen based on the transition planning objectives for adolescents with autism, as identified in the needs assessment (Fig. 1). For example, fostering self-determination through high expectations is linked to the outcome of self-determination, and having a strong transition team is linked to measuring learning climate. As the BOOST-A™ was developed based on these objectives, the aim was to determine if it was effective in bringing about change in these areas. Particular emphasis was placed on each measure’s sensitivity to detect change. The outcome measures are all self-report, eliminating the risk of assessor bias. All of the outcome measures were trialed in Pilot A with six adolescents on the autism spectrum and their parents to ensure they were appropriate for use with these groups. Modifications were required for two of the questionnaires, as described below.

##### Primary outcome measure

The adolescent’s self-determination will be measured by the AIR Self-Determination Scale (AIR) [55], including their ability, knowledge and perceptions about their self-determination, and what opportunities exist for them to use their knowledge and abilities at home and school. Self-determination has been chosen as the primary outcome measures, as high self-determination is correlated with successful transition to employment in adolescents on the spectrum [25, 27–30]. The AIR consists of 24 items, as well as some free-form, short-answer questions. The AIR has good test–retest reliability (*r* = .74 based on two administrations three months apart), internal consistency (split half test *r* = .95), and construct validity (four factors explained 47% of the variance) [55]. Sensitivity to change was demonstrated in previous studies that used the AIR as an outcome measure for students with disabilities [56, 57]. The AIR has been established as a reliable instrument to use with adolescents on the autism spectrum [58].

##### Secondary outcome measures

Career planning and exploration will be measured by the Career Development Inventory—Australia (CDI-A) [60]. Career planning and exploration is defined as the ability to explore one’s skills and interests in relation to work, and to seek information related to one’s career to assist in making an informed decision [59]. The first two sections of the CDI-A [60] will be used for this trial as they specifically target career planning and exploration. These two sections contain 18 items and are valid and reliable, independent from the entire CDI-A [60]. The CDI-Australia has been found to have adequate internal consistency (career planning α = .84; career exploration α = .63), concurrent validity (*r* = .6–.8), and construct validity (four factors explaining 44.7% of the variance) [61].

Quality of life will be measured by the Personal Wellbeing Index-School Children (PWI-SC) [62], which is based on the Subjective Wellbeing Homeostasis Theory [63], which asserts that an individual operates to maintain their wellbeing around an average point. The PWI-SC contains seven items; one for each of the seven domains: standard of living, personal health, achievement in life, personal relationships, personal safety, community-connectedness, and future security [62]. The PWI-SC has high internal consistency (α = .82) and construct validity (comparative fit index = .96) [64]. Sensitivity to change was demonstrated in a study that used the PWI-SC as an outcome measure for a youth support program [65].

Environment support will be measured using the Learning Climate Questionnaire (LCQ) [66], which measures an individual’s perception of support from their team, or the environmental aspects that contribute to the development of self-determination. The LCQ consists of 15 items, and has been found to have good construct validity (one factor explaining 63% of the variance) and high internal consistency (α = .96) [66]. The LCQ has been used to evaluate how instructor’s support impacts on students’ learning in college, demonstrating its sensitivity to change [67]. Based on feedback from Pilot A, the LCQ was adapted to meet the needs of adolescents on the autism spectrum and to ensure it was transition planning specific by removing three questions and slightly modifying the language.

Domain specific self-determination was measured by the Transition Planning Objectives Scale (TPOS). The TPOS was designed specifically for this trial, because the authors could not identify an existing standardized tool that comprehensively evaluated the transition planning objectives identified in the needs assessment (Fig. 1). The primary researcher (MH) developed the scale based on the transition planning objectives and the measure of processes of care (MPOC) [68]. The MPOC was designed to assess parents’ perceptions of the care provided to their children by health professions in rehabilitation centers. Its underlying concepts align with those of the transition planning objectives, including enabling partnerships and family-centered care. The TPOS consists of 16 items, each of which addresses an objective in Fig. 1. Each item is rated on a 10-point Likert scale, anchored by strongly disagree to strongly agree. The measure was reviewed by the research team and then piloted with six adolescents on the autism spectrum and their parents, after which minor modifications were made. Since the validity and reliability of the transition planning objectives scale is not yet known, the data obtained from this measure will be interpreted and reported with caution. In addition, it is recommended that future studies aim to validate this outcome measure.

##### Statistical analysis

Simple descriptive statistics (frequencies and percentages for categorical variables; means, standard deviations, ranges for continuous variables) will be used to summarize the demographic and baseline profiles of participants. These baseline variables will include the assessment of autism severity (using the SRS-2), and the outcome measures described above. The Chi square or *t* test (as appropriate) will be used to compare the profiles of participants between the intervention and control groups. If any continuous data are found to be not normally distributed (from the Kolmogorov–Smirnov test), these data may either be transformed to improve their normality or analyzed using an appropriate non-parametric test.

Effectiveness of the intervention for the AIR, the primary outcome, will be determined by calculating the change from Time point 1 to Time point 2, and comparing the changes within and between intervention and control groups using dependent and independent *t* tests (or non-parametric Wilcoxon signed rank tests and Mann–Whitney U test if the data are not normally distributed). If the analysis reveals differences in baseline characteristics between the intervention and control groups, the analyses will be adjusted for these differences using a general linear model (GLM). Analysis of secondary outcomes will be performed using a multivariate ANOVA (MANOVA). Analyses will be performed using an intention-to-treat strategy, where participants will be classified as belonging to the group (intervention or control) to which they were initially allocated, regardless of the treatment they actually received. Participants who do not provide outcome data at Time point 2 will still be included in the trial, and their Time point 1 data will be used for Time point 2 to allow for intention-to-treat analysis of the data. The Statistical Package for the Social Sciences (SPSS v.22) will be used to analyze the data, and a p value of .05 will be used as the level of statistical significance in all inferential analyses.

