### Objectives of the trial

The hypothesis for the trial is that the BOOST-A™ will improve self-determination in adolescents on the autism spectrum transitioning to post-school life. The objectives of the trial are to:determine the effectiveness of the BOOST-A™ in improving self-determination in adolescents on the autism spectrum; anddetermine the effectiveness of the BOOST-A™ in improving quality of life; access to environmental supports; career planning and exploration; and vocational exploration among adolescents on the autism spectrum.

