### Trial design and procedures

A controlled clinical trial [47] will be used to determine the effectiveness of the BOOST-A™ in improving the self-determination of adolescents on the autism spectrum; and in improving their outcomes of quality of life, access to environmental supports, and career planning skills. The trial will be a cluster group, two-arm, superiority trial with 1:1 allocation ratio. The trial will aim to detect any difference in these outcomes between participants in the intervention group (BOOST-A™) and a control group. Figure 2 shows the schedule of enrolment, intervention, and assessment for the trial. Participants in the intervention group will complete the BOOST-A™ at home and/or at school. Participants will complete the BOOST-A™ over a period of 12 months. This timeframe was chosen to ensure the participants have adequate time to complete all four modules, including the initial team meeting and at least one review meeting. Adherence will be monitored via website analytics, including number of modules completed and number of logins to the BOOST-A™ website. Participants allocated to the control group will participate in the existing post-school planning process used at their school (regular practice).

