##### Sample size

Altman’s nomogram equation was used to determine the sample size. A total sample of n = 80 (n = 40 in each group) would be the minimum required to identify a standardized difference of 0.6 (i.e., Cohen’s *d*) [53], with a power of 80% and a critical alpha value of .05.

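### Within-group paired tests are part of how effectiveness on the primary AIR is determined, with no rule for discordant results, so a 12-month rise in the BOOST-A arm alone could be claimed as an effect

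*Protocol article*

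**What the plan says.** In the protocol article, the Statistical analysis section sets the rule for the primary outcome. It begins "Effectiveness of the intervention for the AIR, the primary outcome, will be determined by calculating the change from Time point 1 to Time point 2". Later words of that sentence name the method, "comparing the changes within and between intervention and control groups using dependent and independent" *t* tests. The fallback has the same two parts: "non-parametric Wilcoxon signed rank tests and Mann–Whitney U test if the data are not normally distributed". One significance level covers everything: "a p value of .05 will be used as the level of statistical significance in all inferential analyses".

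Three tests therefore sit inside the sentence that determines effectiveness: a paired test in each arm and an independent test between arms. The section does not rank them, does not say whether one or all must be significant, and does not say how to read disagreement.

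Other sections point to the contrast between arms. Trial design and procedures describes a two-arm superiority trial and says "The trial will aim to detect any difference in these outcomes between participants in the intervention group (BOOST-A™) and a control group". The Sample size section gives 40 per group as the "minimum required to identify a standardized difference of 0.6", "with a power of 80% and a critical alpha value of .05". Objectives of the trial states the hypothesis as "the BOOST-A™ will improve self-determination in adolescents on the autism spectrum transitioning to post-school life".

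**The concern.** Only the comparison between arms answers a superiority question. A paired test in the BOOST-A arm asks whether scores moved over 12 months. In students in school years 8 to 11, that movement combines any program effect with maturation, schooling, regression to the mean and repeat testing. The control arm is there to remove these. The article itself gives reason to expect some movement in both arms: controls follow their school's existing planning process, and the Background links transition planning to better self-determination.

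Reporting a paired test for each arm also invites the argument that BOOST-A works because its arm changed significantly and the control arm did not. That is not a test of a difference between arms.

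At stake is the headline conclusion on the primary outcome. Under Ethics, consent and permissions, the offer of BOOST-A to control participants also depends on its having been shown effective.

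**Working it through.** **The plan's own figure.** For a standardized difference of 0.6, two-sided .05 and 80% power, the usual formula gives a total of 4(1.96 + 0.842)²/0.6² ≈ 87.2, or 44 per arm. Power with 40 per arm is 76.5% by the normal approximation (75.5% by the *t* distribution). The stated 80 is not reproduced exactly, but a nomogram is read by eye. This is a separate matter and does not affect the present point. The calculation is for two groups; no paired test is sized.

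**Inputs for the check**
- *n* = 40 per arm (Sample size).
- Alpha .05 (Statistical analysis). Two-sided is assumed, because the article does not say.
- Correlation *r* between baseline and 12 months: .74 is the AIR's three-month retest figure (Primary outcome measure). No 12-month value is given, so .5 and .9 are also shown.
- Common rise *d* in both arms, in baseline SDs: the article gives none. Values of 0.1, 0.2 and 0.3 are assumed.
- BOOST-A effect: zero. Participants independent, complete data.

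**Formulas.** The SD of change is √(2(1 − *r*)) baseline SDs, so √0.52 = 0.721 at *r* = .74 and 1 at *r* = .5. The paired *t* statistic in one arm has 39 degrees of freedom and noncentrality *d*√40 / SD of change. At *r* = .74 this is 0.1 × 6.325 / 0.721 = 0.877 for *d* = 0.1, then 1.754 and 2.631 for 0.2 and 0.3. At *r* = .5 it is 0.632, 1.265 and 1.897.

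**Chance that the BOOST-A arm's paired test is significant and favourable although BOOST-A does nothing** (noncentral *t*, confirmed by simulation of 40,000 trials per setting):

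| Common rise | *r* = .5 | *r* = .74 | *r* = .9 |
|---|---|---|---|
| 0.1 SD | 9% | 13% | 28% |
| 0.2 SD | 23% | 40% | 79% |
| 0.3 SD | 46% | 73% | 99% |

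With no common rise the figure is 2.5% at every *r*.

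**The other readings, same simulation**
- Between-arm test alone: two-sided rejection stays at about 5% in every setting (about 2.5% favouring BOOST-A), because a rise common to both arms cancels.
- Significant rise in the BOOST-A arm but not in control: 12%, 24% and 20% of trials at *r* = .74 for the three rises; 8%, 18% and 25% at *r* = .5.
- Both the BOOST-A paired test and the between-arm test required, favourable: 1.9%, 2.5% and 2.4% at *r* = .74. This rule does not inflate the error.

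The error rate therefore depends on which rule is meant, and the text does not say.

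**The case against.** The strongest reply is that the article, read as a whole, already identifies the confirmatory contrast. The stated aim is a difference between arms, the sample size is for two groups, and adjusting for baseline differences by a general linear model only serves a between-group comparison. The valid test is planned, and a ranking of tests is a detail that a condensed article may leave to an analysis plan. Most of this stands, and it is why the remedy is small. But the point is not a missing detail. The article writes out how effectiveness is determined and places the paired tests in that sentence.

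Several stronger readings are tempting and are not supported:
- A reader might infer that the trial's false-positive rate *is* 13% to 73%. Those figures require the paired test to suffice alone and a rise that the article does not give. If both tests were required, there would be no inflation.
- A reader might count significance on any of the three tests as a false positive. A significant change in the control arm, or a decline in either arm, would not be read as a BOOST-A benefit, so that count is not an error rate for the claim.
- A reader might say that a within-arm rise satisfies the hypothesis. The hypothesis attributes the improvement to the program, and the stated aim compares arms. The loose wording makes such a claim possible but does not endorse it.
- A reader might take 5% as established for the planned between-arm test. It holds under independence, whereas Treatment allocation puts students of the same school in the same arm.

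Carrying baseline values forward for missing follow-up would shrink the mean change and alter the percentages. It would not turn a paired test into a comparison of arms.

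**Conclusion.** The concern holds as a defect in the written decision rule for the primary outcome. The between-group contrast appears to be intended, but the text allows a significant 12-month rise within the BOOST-A arm to be presented as effectiveness, and it gives no rule for discordant results. How far this could mislead depends on the unstated natural rise, on the 12-month correlation, and on whether the paired test may count alone. On that last condition, a common rise of only 0.2 SD would give a spurious favourable result in 23% of trials at *r* = .5 and 40% at *r* = .74. The existence of the defect does not depend on these assumptions; only its size does.

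**What to change.** In Statistical analysis, state that effectiveness on the AIR is decided solely by the between-group comparison of AIR change, or of the Time point 2 AIR score adjusted for baseline AIR. Choose one of the two in advance and report it as one estimated difference with its 95% confidence interval and *p* value. Remove the dependent *t* tests and Wilcoxon signed-rank tests from the determination of effectiveness. Label within-group changes as descriptive and not as evidence of effect.

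The deciding comparison should not become an unadjusted comparison of Time point 2 scores. Allocation alternates and is not randomized, so that would drop the planned change score and let baseline imbalance pass into the estimate.

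The cost is a few sentences, with no extra data or participants. It should be settled before the AIR outcomes are analysed. The small downside is that an improvement within the BOOST-A arm can no longer be presented as effectiveness.

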##### Treatment allocation

Following initial screening, potential participants will be allocated to either the intervention or control group according to the order in which they register interest. The first participant will be allocated to a group based on a coin toss completed by a researcher who will not be directly involved in liaising with participants. The exception to this allocation scheme is that if a newly enrolled participant is attending a school that a previously or currently enrolled trial participant attends, then the newly enrolled participant will be allocated to the same treatment group as the previous student. The reason for this is to reduce the risk of contamination, since school staff will be involved in administering the intervention. Participants will be blinded to their treatment; however, non-blinded allocation and lack of randomization could introduce potential bias. Once allocated to a group, participants will be sent the participant information and consent form. Forms for the intervention group will differ slightly from those for the control group, as they will contain information about the BOOST-A™, to ensure blinding to treatment is maintained. Participants who provide written consent will then be assigned a unique participant identification number. A strength of the trial is that the BOOST-A™ will be administered by parents and professionals who are not a part of the research team, thereby minimizing researcher bias. In addition, the primary researcher will have minimal information about the participants at time of randomization.

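### Schoolmates are always placed in the same arm, but the planned tests treat every pupil as independent; if schools contribute several pupils whose change scores are correlated, type I error exceeds .05

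*Protocol article*

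**What the plan says.** Three sections of the Protocol article bear on this.

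- **Trial design and procedures** gives the design label: "The trial will be a cluster group, two-arm, superiority trial with 1:1 allocation ratio". The control condition is whatever post-school planning the pupil's own school already runs.
- **Treatment allocation** starts from individuals, who are "allocated to either the intervention or control group according to the order in which they register interest", the first by coin toss. It then makes an exception. If a new participant attends a school that already has a participant, "then the newly enrolled participant will be allocated to the same treatment group as the previous student". The reason given is "to reduce the risk of contamination, since school staff will be involved in administering the intervention".
- **Statistical analysis** names the primary method: change in the AIR from Time point 1 to Time point 2, "comparing the changes within and between intervention and control groups using dependent and independent" t tests. Wilcoxon signed rank and Mann–Whitney U tests are the fallback for non-normal data. A GLM is used if the groups differ at baseline, and a MANOVA covers the secondary outcomes. The significance level is .05 throughout.

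No school effect, cluster-robust error or school-level summary is named. The **Sample size** section ("A total sample of n = 80 (n = 40 in each group) would be the minimum required") uses an individual-level calculation with no cluster size, ICC or design effect.

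**The concern.** The allocation rule guarantees that pupils from one school never split across arms. Whatever schoolmates share in their change over the year therefore cannot cancel between arms and becomes part of the treatment contrast. An independent t test computes its standard error as though that shared part did not exist.

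The article itself gives reasons to expect a shared part. School staff help to administer the intervention, regular practice in the control arm belongs to the school, and the AIR asks partly about opportunities at school.

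At stake is the one confirmatory comparison for the primary hypothesis. With positive within-school correlation the error runs one way, towards false positives and intervals that are too narrow. This is not a detail that an article may leave to an analysis plan: the article names the test, and the test conflicts with the allocation that the article describes.

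**Working it through.** **Inputs from the article.** 40 pupils per arm, standardized difference 0.6, power 80%, alpha .05 (sidedness not stated).

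**Assumed, because the article gives neither.** The size-weighted mean number of pupils per school, m = Σ(size²)/Σ(size), and the ICC of *change scores*, taken as 0.05 to 0.20.

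**The plan's own figure.** The two-sided normal approximation gives 2 × (1.960 + 0.842)² / 0.6² = 43.6, so 44 per arm and 88 in total, not 80. At 40 per arm power is 76.5%. The gap may come from reading a nomogram. It is separate from this point and matters here only because 76.5% is the starting value for power below.

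**Formulas.**
- Design effect: DE = 1 + (m − 1) × ICC
- True standard error = t-test standard error × √DE
- Actual two-sided alpha ≈ 2 × [1 − Φ(1.96/√DE)]
- Power of an analysis that allows for school ≈ power with 40/DE per arm

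**School patterns tried, per arm.**
- 30 single-pupil schools and 5 pairs: m = (30×1 + 5×4)/40 = 1.25
- 20 single-pupil schools and 10 pairs: m = (20×1 + 10×4)/40 = 1.5
- 20 single-pupil schools and 4 schools of five: m = (20×1 + 4×25)/40 = 3.0

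**One case in full.** For m = 3 and ICC 0.10, DE = 1 + 2 × 0.10 = 1.20 and √DE = 1.095. Then 1.96/1.095 = 1.79 and alpha ≈ 0.074.

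**Results for ICC 0.05 / 0.10 / 0.20** (simulation: 20,000 trials per cell)

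| m | DE | alpha, formula | alpha, simulated | power (from 76.5%) |
|---|---|---|---|---|
| 1 | 1.00 | 0.050 | not run | 76.5% |
| 1.25 | 1.01 / 1.03 / 1.05 | 0.051 / 0.053 / 0.056 | 0.051 / 0.055 / 0.057 | 76.0 / 75.5 / 74.5% |
| 1.5 | 1.03 / 1.05 / 1.10 | 0.053 / 0.056 / 0.062 | 0.054 / 0.057 / 0.060 | 75.5 / 74.5 / 72.5% |
| 3 | 1.10 / 1.20 / 1.40 | 0.062 / 0.074 / 0.098 | 0.061 / 0.074 / 0.096 | 72.5 / 68.8 / 62.1% |

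A separate simulation gave 0.054 to 0.060 at m = 1.5 and 0.062 to 0.095 at m = 3.

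**A few larger schools only.** With all other schools single, one school of four in one arm leaves alpha at about 0.05. Two schools of five in one arm give 0.051 to 0.061.

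**The case against.** The strongest reply is that the problem may be small in this trial. Pupils register one at a time from across Australia through social media, websites, flyers and referral, and home-schooled pupils are eligible. Allocation alternates individuals, and the same-school rule is described as an exception, so many schools may contribute one pupil. The outcome is also a change score, so stable differences between schools cancel and only school-level differences in *change* count. All of this stands, and it points towards the upper rows of the table. It does not remove the conflict: nothing caps the number of pupils per school, and schools themselves are asked to email potential participants.

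Four stronger readings are tempting but not supported.

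- *The standard errors are certainly too small.* This needs schools with two or more pupils and a positive correlation of change scores. The article documents neither.
- *A positive result could be an artefact of one or two multi-pupil schools.* The last calculation above speaks against this: one or two such schools barely move the error rate.
- *Schoolmates share team meetings.* Under the description of the intervention, each adolescent identifies their own team, and the introduction and first two modules are done at home. School staff are involved in administering the program but do not deliver it alone.
- *The change score must give way to baseline-adjusted Time point 2 AIR.* That may be worth discussing, but clustering does not require it.

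**Conclusion.** The mismatch between allocation and analysis is real; its size is conditional. The planned tests exceed .05 if some schools contribute two or more pupils and change scores correlate positively within school. That correlation is plausible, because both the intervention and regular practice run partly through the school.

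For an assumed ICC of 0.05 to 0.20 and 40 per arm, actual alpha is about 0.054 to 0.060 at a weighted mean school size of 1.5 and about 0.06 to 0.095 at 3. If every school has one pupil there is no effect. The article does not show where the trial falls in this range. The point should be fixed before the outcome data are analysed, and it becomes essential if several multi-pupil schools are enrolled.

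**What to change.** Account for school in the between-group analyses of the AIR and of the secondary outcomes.

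- Fit a mixed model to the change score with arm as a fixed effect, any baseline adjustment already planned, a random school intercept and small-sample (for example Satterthwaite) degrees of freedom.
- If most schools have one pupil, the school variance may be poorly identified or estimated at zero. State in advance that cluster-robust standard errors with a small-sample correction will then be used.
- Treat single-pupil schools and home-schooled pupils as clusters of one.
- If a non-parametric fallback is kept, it must also respect school.
- Report the number of schools, the pupils per school and the ICC.

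The cost is revised wording, a modest amount of modelling and slightly wider intervals. No new data are needed: the allocation rule cannot be applied without knowing each pupil's school, so the identifier only has to be carried into the analysis file. If clustering proves negligible, the result will barely change.

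### The primary AIR analysis defaults to an unadjusted change-score t test, and baseline tests and a normality test may alter it; precision is lost and imbalance may go unadjusted

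*Protocol article*

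**What the plan says.** All of this is in the Statistical analysis section of the protocol article unless stated otherwise.

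- **Default test.** Effectiveness on the AIR "will be determined by calculating the change from Time point 1 to Time point 2", and the changes are compared between groups by an independent t test. Baseline AIR is not a covariate.
- **Adjustment rule.** Baseline profiles, which include the outcome measures themselves, are compared by chi-square or t test. Then: "If the analysis reveals differences in baseline characteristics between the intervention and control groups, the analyses will be adjusted for these differences". This adjustment is to be made in a general linear model. The section sets .05 as the significance level for all inferential analyses, so a difference is naturally read as a significant one.
- **Normality rule.** If the Kolmogorov–Smirnov test finds continuous data non-normal, "these data may either be transformed to improve their normality or analyzed using an appropriate non-parametric test". For the AIR, the Mann–Whitney test is named as the alternative to the between-group t test.
- **Candidate covariates.** The Data collection section says "Additional independent variables for this trial will be comorbidities (including mental health), gender, age, and socioeconomic status". It also collects the SRS-2, year level and postcode. The analysis section does not commit to using any of these in the primary model.
- **Size.** The Sample size section gives "A total sample of n = 80 (n = 40 in each group) would be the minimum required" for a "standardized difference of 0.6", "with a power of 80% and a critical alpha value of .05".

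**The concern.** The form of the primary comparison is not settled until baseline and distributional tests have been run. Covariate set, scale and test can each change in the light of the data. The baseline tests are a poor guide to what needs adjusting. With 40 per arm they miss moderate imbalances, and a variable that reaches significance need not predict the AIR. The wording of the normality rule leaves the choice between transformation and a rank test open, and a Mann–Whitney test cannot carry the linear-model adjustment. If the data are non-normal and baseline also differs, the reader cannot tell which analysis is primary.

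The design raises the stakes. Allocation follows the order of registration, with same-school participants kept together, and the Treatment allocation section itself concedes that the lack of randomization could introduce bias. Baseline differences therefore need not be chance ones, and covariate adjustment is one of the few safeguards available. At stake are precision on the single primary outcome, imbalance left in the estimate, and a clearly defined primary result.

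**Working it through.** **Inputs.** From the protocol: 40 per arm, effect 0.6, alpha .05 (two-sided assumed, since sidedness is not stated), and AIR test–retest r = .74 over three months (Primary outcome measure section). Assumed: r = .5 as a lower 12-month value, because no 12-month correlation is given, and equal variances at both time points. School clustering and the carrying forward of Time point 1 scores are not modelled.

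**The plan's own figure.** For d = 0.6 and 80% power, a two-sided calculation needs 44 per arm (normal approximation) or 45 per arm (t), so 88 or 90 in total. With 40 per arm, power is 76.5% (normal) or 75.5% (t). The stated 80 is not reproduced. It was derived by nomogram, so graph reading may explain the gap. That is a separate point; the 75.5% serves here as the base.

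**Precision.** In units of the AIR variance, the change score has variance 2(1 − r) and ANCOVA has residual variance 1 − r². The ratio ANCOVA/change is (1 + r)/2.

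| r | Variance ratio | Change-score SE relative to ANCOVA, √(2/(1 + r)) |
|---|---|---|
| .3 | 0.65 | 1.24 |
| .5 | 0.75 | 1.15 |
| .74 | 0.87 | 1.07 |
| .9 | 0.95 | 1.03 |

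**Power at 40 per arm (noncentral t, two-sided).** The protocol does not say which SD the 0.6 refers to, so both readings are shown.

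| Reading of 0.6 | r | Change score | ANCOVA |
|---|---|---|---|
| Change-score SDs: ANCOVA effect 0.6/√((1 + r)/2) | .74 | 75% | 81% |
| | .5 | 75% | 86% |
| AIR-score SDs: effects 0.6/√(2(1 − r)) and 0.6/√(1 − r²) | .74 | 96% | 98% |
| | .5 | 75% | 86% |

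**What the baseline test misses.** The largest non-significant baseline AIR difference is t(.975, 78 df) × √(2/40) = 1.991 × 0.2236 = 0.445 SD. If it arose by chance, it shifts the change-score contrast by (1 − r)D: 0.26 × 0.445 = 0.12 SD at r = .74, and 0.5 × 0.445 = 0.22 SD at r = .5. A true imbalance of 0.3 SD is detected 26% of the time, and one of 0.5 SD 60% of the time.

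**What the conditional rule recovers.** In a simulation with 40 per arm, 40,000 runs, a pre-test on baseline AIR only, r = .5 and a true effect of 0.6 AIR SDs, adjustment was triggered in about 5% of trials. Power was 75.6% for the change score, 76.6% for the conditional rule and 86.1% for ANCOVA in every trial. With no true effect, the conditional rule rejected in 4.4% of trials (r = .5) and 4.7% (r = .74).

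**Chance triggers.** With k independent baseline tests at .05, the probability of at least one is 1 − .95^k: 23% for k = 5 and 40% for k = 10. The number of tests is an assumption.

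**The case against.** Several counter-arguments have force.

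- **The change score is itself prespecified.** A reader might infer that the whole primary model is chosen after the data are seen. The document does not support that. Only the covariate rule and the normality rule depend on the data, and the case against the change score as the default is one of efficiency.
- **Type I error.** A reader might infer that the pre-tests inflate it. Nothing shows this. The single pre-test simulation gave 4.4% to 4.7%. One with ten baseline tests, adjusting for every significant variable (40 per arm, randomised, 8,000 runs), gave 4.0% to 4.9%. The normality switch was not simulated.
- **Bias.** The (1 − r)D shift treats the imbalance as chance that regresses to a common mean. Allocation here is not randomised. If the groups differ stably and would have moved in parallel, the change score removes the difference and ANCOVA on an imperfectly reliable baseline would be the biased method. It is therefore not established that the change score over-corrects.
- **Size.** At the only correlation quoted, the penalty is 7% in standard error, and on the AIR-score reading power moves only from 96% to 98%. Carrying scores forward raises the analysed correlation: with an assumed 20% dropout, .74 becomes 0.8 × .74 + 0.2 = .79, and the variance ratio about 0.90.
- **Chance triggers.** Independence is generous. With assumed pairwise correlations of .3 to .5 among ten tests, the probability falls from 40% to between 29% and 36%. A trigger also only adds a baseline covariate.
- **Rank test and adjustment.** The protocol assigns adjustment to the linear model, not to the Mann–Whitney test, so this is an unclear sequence and not a strict contradiction.

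These points limit the size and the wording. None of them defends letting baseline significance tests and a Kolmogorov–Smirnov test select the primary model. Nor does an unseen analysis plan answer the point, because these are rules the article states.

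**Conclusion.** The point holds in a limited form. The default primary analysis forgoes an adjustment that is available at almost no cost, and two data-dependent rules can alter it. The change-score standard error is 7% larger than ANCOVA's at r = .74 and 15% larger at r = .5. The power gain ranges from 2 to 11 percentage points, depending on the 12-month correlation and on which SD the 0.6 refers to, neither of which the protocol gives. A baseline AIR difference of up to 0.45 SD could stay unadjusted, shifting the contrast by 0.12 to 0.22 SD against a target of 0.6, provided that the imbalance is a chance one. The conclusion is lost precision, possible residual imbalance and an unclear primary analysis when both rules apply. It is not that the p-value is invalid or that the change score is necessarily biased. This should be fixed, but it does not by itself undermine the trial.

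**What to change.** Prespecify one primary model: AIR at Time point 2 regressed on arm and baseline AIR, plus a short named list of covariates already collected, for example SRS-2 score, age or year level, gender and socioeconomic status. Report the adjusted mean difference with its 95% confidence interval whatever the baseline or normality tests show. Present baseline data descriptively, and drop the baseline significance tests and the Kolmogorov–Smirnov switch as model selectors.

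Because allocation is not randomised, give the change-score comparison as a sensitivity analysis. If residuals look poor, add a rank-based, bootstrap or robust-standard-error result, also as sensitivity.

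The cost is a change of wording and a few degrees of freedom; no new data are needed. It should be settled before group comparisons are seen. How the model handles school clustering is a separate point.
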